### Criteria for discontinuing or modifying allocated interventions {11b}

Participants can withdraw at any point if a participant in either arm indicates that they wish to discontinue the trial. In this case, they will only be contacted further by the research team to invite them to take part in a brief written survey to ascertain their reasons for not taking part. However, the participants will have no intermediate levels of discontinuation of the trial.

We will assess whether it is in the participant’s best interest to continue or discontinue trial treatment if a serious adverse reaction occurs. In such cases, discontinuation of the intervention will be recommended. If an unexpected serious adverse reaction is linked directly to trial participation or treatment, the trial will be temporarily halted for investigation. If future risk cannot be mitigated, the trial will be discontinued. The sponsor, ethics committee chair, and principal investigator will lead this process. The same protocol will be followed if information surfaces indicating that the therapy intervention or trial procedures are unsafe.

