### Provisions for post-trial care {30}

The patients’ clinical teams will be informed in writing of their participation at the end of the trial. There is no anticipated harm or compensation for trial participation.

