### Adverse event reporting and harms {22}

#### Risk monitoring

To identify potential risk issues, our research assistants will conduct a screening every 48 h after the completion of the intervention sessions. This screening will involve checking the skin condition on the skull where the electrodes were placed and mild headache. These cautions are important to ensure no adverse effects or complications from the intervention and mitigate potential risks to the participants.

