#### Adverse event and serious adverse event recording and reporting

Possible adverse events and other unintended effects of the trial will be documented in the medical records and periodically reported to the Scientific Ethics Committee. The expected hazards in this trial, according to safety guidelines, were skin damage on the skull where the electrodes were placed and mild headache. If unexpected events occur, we will use MedDRA in the trial publication to report all adverse events. Lethal or severe adverse events will be reported to the Health Services of the Region of Valparaíso (Chile) and the Scientific Ethics Committee as soon as possible or within 7 days of getting informed of the adverse event.

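### The halt rule is triggered by unexpected serious reactions, but the time-limited report is triggered by lethal or severe events, and the only active safety screen asks about the two expected hazards.

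*Protocol article*

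**What the plan says.** Four statements in the protocol article bear on this point.

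- **Halt rule, section {11b}.** "If an unexpected serious adverse reaction is linked directly to trial participation or treatment, the trial will be temporarily halted for investigation". On who runs it: "The sponsor, ethics committee chair, and principal investigator will lead this process". There is also a general trigger: "The same protocol will be followed if information surfaces indicating that the therapy intervention or trial procedures are unsafe". For a single participant with a serious adverse reaction, the section first says the team will weigh whether continuing or stopping serves that person best. It then says that stopping will be recommended in such cases.
- **Active screen, section {22}, Risk monitoring.** "our research assistants will conduct a screening every 48 h after the completion of the intervention sessions". Its content is given as: "This screening will involve checking the skin condition on the skull where the electrodes were placed and mild headache".
- **Time-limited report, section {22}, Adverse event and serious adverse event recording and reporting.** "Lethal or severe adverse events will be reported to the Health Services" of the region and to the ethics committee, "as soon as possible or within 7 days of getting informed of the adverse event".
- **General recording, same subsection.** Possible adverse events and unintended effects go into the medical records and are passed to the ethics committee periodically, with no interval stated. Skin damage at the electrode sites and mild headache are named as the expected hazards. For unexpected events the one specific provision is MedDRA coding in the publication.

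**The concern.** The halt rule turns on three attributes of a reaction: that it is serious, unexpected and related to the trial. The criterion for the time-limited report uses none of them. It uses death or severity. Severity grades how intense an event is, whereas seriousness is a separate classification, and an event of moderate intensity can be serious. The two rules therefore select overlapping but different sets of events, although the ethics committee chair has a part in both.

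The screen adds to this. It is the only active check the article describes, and it asks about exactly the two hazards already expected. The halt rule concerns reactions that were not expected.

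Two members of staff following {11b} and {22} could route the same event differently, and one of the three people named to lead a halt could hear of it late. Unexpected symptoms would also be ascertained less systematically than the two listed ones, which weakens the harms comparison between arms.

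**Working it through.** The plan gives no figure to reproduce, so the first step sets the sections side by side and the second counts exposure.

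**Step 1. Which events each rule covers**

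| Rule | Criterion | Time limit |
|---|---|---|
| Trial halt, {11b} | Unexpected, serious, linked directly to the trial | None stated |
| General halt trigger, {11b} | Information that the therapy or procedures are unsafe | None stated |
| Time-limited report, {22} | Lethal or severe | As soon as possible, or 7 days from being informed |
| General recording, {22} | Possible adverse events and unintended effects | Periodic, interval not stated |
| Active screen, {22} | Skin condition, mild headache | Every 48 h after sessions |

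Take a reaction that is serious, unexpected and related, but not severe. It meets the halt criterion and fails the time-limited criterion. Its only stated route to the ethics committee is the periodic report. Unless it shows as a skin change or headache, the active screen does not ask about it.

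**Step 2. What the 7-day limit could mean in sessions**

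Inputs, from section {11a}: sessions run twice a week for 6 weeks, 12 in all, with stimulation in sessions 3, 4, 5, 6, 7, 8, 9 and 11. Assumptions: the weekly pattern is regular, and the team learns of the event on the day of session *s*.

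With two sessions a week in a regular pattern, session *s* + 2 falls exactly 7 days after session *s*. Sessions *s* + 1 and *s* + 2 therefore lie within 7 days, or only *s* + 1 if day 7 itself is excluded. Counting the stimulated ones:

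| Event at session | Sessions within 7 days | Stimulated, day 7 included | Stimulated, day 7 excluded |
|---|---|---|---|
| 3 to 7 | *s* + 1, *s* + 2 (both between 4 and 9) | 2 | 1 |
| 8 | 9, 10 | 1 | 1 |
| 9 | 10, 11 | 1 | 0 |
| 11 | 12 | 0 | 0 |

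The counts are the same for within-week gaps of 3 and 4, 2 and 5, or 1 and 6 days. They are upper bounds per participant still in treatment, and they apply to events that do carry the 7-day limit. For the reaction in step 1 no such count can be made, because the interval of the periodic report is not stated.

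**The case against.** The strongest reply is that the article has wider safety nets than the two rules alone suggest, and much of this stands.

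- A reader might infer that a serious but non-severe reaction would never reach the ethics committee. The text does not support that. Possible adverse events and unintended effects are reported to it periodically, so only the speed is open.
- A reader might infer that the comparison of harms is limited to skin changes and headache. That also fails. General recording covers other events, and all adverse events are to be reported with MedDRA if unexpected ones occur. What is limited is the active questioning.
- A reader might treat 7 days as a wait before the trial can be halted. It is an outer limit on reporting to outside bodies. The sponsor and principal investigator co-lead the halt and can act at once, and the general trigger in {11b} needs no serious or severe label. For the affected participant, {11b} says stopping will be recommended. Multiplying the session count across a treatment group would assume that nobody on site acts.
- Section {30} says "There is no anticipated harm or compensation for trial participation". It concerns care after the trial and is weak evidence of a contradiction with the expected hazards in {22}.
- The lethal or severe sentence stands under a heading that names serious adverse events, so *severe* may simply be loose wording for *serious*. Definitions and the method of eliciting events may also sit in the full protocol, and their absence from the article is no finding.

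The last reply explains the mismatch but does not remove it. The article prints a halt trigger, a reporting criterion and the content of a screen, and as printed these do not fit together. If *severe* was meant as *serious*, the correction is easy.

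**Conclusion.** The point holds as an inconsistency between {11b} and {22}, together with a gap in active questioning. A reaction that is serious, unexpected and related, but not severe, meets the halt rule yet has no stated fast route to the ethics committee, whose chair co-leads the halt. Unexpected events depend on general recording and are not actively asked about.

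The size is modest. A lag is possible, not built in. Where the 7-day limit applies, at most 2 further stimulated sessions fall inside it after an event at sessions 3 to 7, and 0 or 1 after later stimulated sessions. This rests on a regular twice-weekly pattern and awareness on the day of the session. Sample size and the primary analysis are untouched.

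The two sentences in {11b} on a single participant can be read as individual assessment with a default, but the text does not say so and should.

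**What to change.** 1. Reconcile {11b} and {22} so that one event class triggers both the halt process and the time-limited report.
2. In {11b}, reconcile the sentence about weighing continuation with the one saying that stopping will be recommended.
3. Add to the existing 48-hour screen, worded identically in both arms, one open question on any other new symptom since the last session.

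The clinical criteria and the times are for the sponsor and ethics committee to set. The cost is a wording amendment and one question at a contact that already takes place. The small downside is more minor events to record and code.

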### Strategies to improve adherence to interventions {11c}

Individual interviews at the beginning of both programmes (CCTP and TCTP) will reinforce the research rationale, highlight the importance of assistance to all treatment sessions and following, and identify potential barriers to participation. We will offer training to help patients familiarise themselves with the technical aspects of computers utilised in the cognitive programmes. We will call to remind each patient before the appointment and will provide transportation to assist on site.

### Relevant concomitant care permitted or prohibited during the trial {11d}

All patients will be encouraged to continue medical controls and treatments as usual.

### Provisions for post-trial care {30}

The patients’ clinical teams will be informed in writing of their participation at the end of the trial. There is no anticipated harm or compensation for trial participation.

### Outcomes {12}

#### Primary outcome

The primary result will be prefrontal theta oscillatory activity. This continuous variable is sensitive to electrophysiological changes underlying cognitive processes as WM. It has been described in several works of our group and others [28, 38–43]. The primary timepoint for outcome measures will be three times: pre-intervention, 1 and 12 weeks post-intervention. This outcome corresponds to the ratio of the normalised power (mean/standard error, mV^2^) of the prefrontal theta oscillation (5–10 Hz, F3 electrode) related to successful memory performance (SMP). This prefrontal theta oscillation is calculated based on a single-trial general linear model that includes SMP as the regressor of interest and memory load as a secondary regressor.

#### Secondary outcomes

Secondary results will correspond to performance measures in validated test work memory tasks:

The secondary timepoint for outcome measures will be three times: pre-intervention, 1 and 12 weeks post-intervention.

(1) WAIS-IV Digit Retention subtest. Chilean standard [44]

It is part of the WM Index and consists of three tasks: (a) Direct Digits: repeat a series of digits, presented orally, in the same order as they are presented; (b) Reverse Order Digits: repeat a series of digits in reverse order as they are presented; and (c) Sequence Digits: order and repeat from lowest to highest a series of numbers read by the examiner. These tasks assess attention and resistance to distraction, immediate auditory memory, and WM.

(2) Trail Making Test B (TMT-B). Chilean standard [45]

This part of TMT reflects mainly WM and, secondarily, the capacity for cognitive flexibility [46]. It connects 25 numbers and letters in ascending order, alternating between them (e.g. 1-A, 2-B, 3-C, etc.). The score is obtained when it takes an individual to complete the task.

(3) Parietal theta oscillatory activity. The ratio of the normalised power (mean/standard error, mV^2^) of parietal theta oscillation (5–10 Hz, CP3 electrode) related to memory load. This parietal theta oscillation is calculated based on a single-trial general linear model that includes memory load as the regressor of interest and successful memory performance (SMP) as a secondary regressor.

#### Baseline survey

Participant characteristics will be assessed as part of the initial evaluation and clinical interview to identify eligible patients who will be invited to participate in the trial. Once selected, participants who have agreed to participate in the trial will be evaluated 1 week before the randomisation with electrophysiological measures and performance in validated test work memory tasks:

### Participant timeline {13}

Potential participants who express interest in the study will undergo a structured on-site interview with the researcher to determine their eligibility for participation. Those who meet the initial screening criteria will be invited for an on-site assessment session, during which they will undergo structured clinical interviews to confirm their eligibility for the study. Eligibility interviews will be conducted immediately after the initial screening. Patients who agree to participate in the trial will then undergo baseline assessments of their electrophysiological measures underlying WM processes, as well as performance measures in validated WM tasks, including the WAIS-IV Digit Retention subtest [44] and the Trail Making Test B (TMT-B) [45]. Baseline assessments will be conducted within 1 week before randomisation. Participants will be randomly allocated and given at least 1 week to become familiarised with the computational devices before the intervention period, which will last 6 weeks. After the intervention period, participants will be assessed again at 1 week and 12 weeks post-intervention. Please refer to Fig. 1 for a schematic diagram of the enrollment, intervention, and assessment schedule.

**Fig. 1 Fig1:**
[figure not shown]
Schedule of enrollment, interventions, and assessments (displayed according to Standard Protocol Ítems: Recommendations for Interventional Trials [SPIRIT])

### Sample size {14}

For the estimation of the minimum required sample size, we will consider the following parameters: (a) Effect size for the mixed ANOVA statistical test (2 × 2, with interaction effects), (b) Statistical power (1 − *β*) = 0.95 and (c) Significance level α = 0.05. We will use the G*Power 3 software to calculate [47]. Considering an effect size *η*^2^ = 0.06, the sample size amounts to 54 participants (n1 = 27; n2 = 27). As our study will be a two-intervention effect, we will consider an effect size somewhat smaller than those observed for comparisons between clinical populations of prefrontal theta oscillations during working memory: for example, Lenartowicz: *η*^2^ = 0.09 [38], and which coincides with the work of our team *η*^2^ ~ 0.1 [28]. The effect size we will use to calculate the sample is considered a moderate to significant effect according to Cohen’s criteria [48]. However, the initial sample size we propose in this project finds the proportion of participants who may present low adherence to the study. In this regard, we can point out that in a preliminary study with similar characteristics, a drop-out rate of about 15% was observed. Therefore, considering the drop-out percentage and the minimum sample size required to investigate an effect, the initial sample will be 62 participants (n1 = 31; n2 = 31).

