The effect sizes will be reported for each electrophysiological and cognitive performance measure analysis through the index η^2^p (partial eta square). The respective post hoc comparisons will use Bonferroni’s correction, and the effect size will be reported through Cohen’s index *d*. Graphs of the interaction effects will be provided if observed. In case of transgression of the sphericity assumption, the Greenhouse–Geisser correction will be made. Consequently, the respective parametric statistics will be provided (i.e. Friedman test, Connover’s post hoc tests). For all hypothesis tests, a significance level will be considered *⍺* = 0.05.

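### The 54 participants give 95% power for about a 1.0 SD arm difference in pre-post change (partial η² about 0.20), not for a partial η² of 0.06; the drop-out allowance also falls slightly short

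*Protocol article*

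**What the plan says.** All in the Protocol article.

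- **Sample size {14}** names the test as "Effect size for the mixed ANOVA statistical test (2 × 2, with interaction effects", with power and significance level given as "0.95 and (c) Significance level α = 0.05", and the tool: "We will use the G*Power 3 software to calculate". At η² = 0.06 it concludes that "the sample size amounts to 54 participants", 27 per arm.
- It justifies the effect by comparison: "we will consider an effect size somewhat smaller than those observed for comparisons between clinical populations of prefrontal theta oscillations during working memory". The cited values are η² = 0.09 and about 0.1. It also describes the chosen effect as moderate or larger by Cohen's criteria.
- It then allows for drop-out of about 15%: "the initial sample will be 62 participants", 31 per arm.
- **Inferential analysis** sets the reporting scale: "The effect sizes will be reported for each electrophysiological and cognitive performance measure analysis through the index", and the index named there is partial η².

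The sample-size section gives neither the correlation between the repeated measures nor the η² convention that was entered.

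**The concern.** In a repeated-measures power calculation, the same η² can stand for very different effects, depending on whether it is scaled by the raw between-person variance or by the error variance of the interaction test. The section presents 0.06 as a moderate effect, sets it beside published values, and attaches 95% power to it. The results will be expressed as partial η². A reader who sees a null result on the primary outcome will then naturally conclude that a partial η² of 0.06 has been excluded with high confidence. Whether 54 completers support that conclusion depends on which scale 0.06 is on.

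**Working it through.** **Inputs.** From Sample size {14}: two groups, two measurements, interaction test (1 numerator df), α = 0.05, power 0.95, η² = 0.06, drop-out 15%, 62 enrolled. Assumed, because not stated: pre-post correlation ρ (0 to 0.8 tried), sphericity ε = 1.

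**1. Reproducing 54.** f² = 0.06/0.94 = 0.0638, so f = 0.2526. In the default option, λ = f²·N·m/(1 − ρ). With N = 54, m = 2, ρ = 0.5: λ = 0.0638 × 54 × 2/0.5 = 13.79, and power on F(1, 52) is 0.954. With N = 52, λ = 13.28 and power is 0.947. So 54 is the smallest even N reaching 0.95.

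| ρ | Smallest even N for 95% | Power at N = 54 |
|---|---|---|
| 0 | 104 | 0.73 |
| 0.3 | 74 | 0.87 |
| 0.5 | 54 | 0.954 |
| 0.7 | 34 | 0.997 |
| 0.8 | 24 | >0.999 |

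Of the correlations tried, only 0.5 returns 54.

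**2. The effect this implies.** The interaction test is a two-sample comparison of change scores, for which λ = N·d²/4, with d the arm difference in SDs of change. Hence d² = 4 × 13.79/54 = 1.02 and d = 1.01. Partial η² = (λ/N)/(1 + λ/N) = 0.2553/1.2553 = 0.203.

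This can be checked without the option or the correlation. With 27 per arm, 95% power requires d = 1.00 (partial η² = 0.25/1.25 = 0.20), and 80% requires d of about 0.78 (0.152/1.152 = 0.13).

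**3. If 0.06 is the partial η² of the pre-post interaction.** Then d = 2f = 0.51. With λ = f²·(N − 2) = 0.0638 × 52 = 3.32, power at 54 is 0.432. With λ = f²·N = 3.45, it is 0.445. Reaching 0.95 needs 208 or 206 completers respectively. If all three visits entered a 2 × 3 interaction with ε = 1, λ = 0.0638 × 52 × 2 = 6.64 on F(2, 104), and power is 0.62.

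**4. The comparison with 0.09 and 0.10.** If those are simple two-group contrasts, they equal 2√(0.09/0.91) = 0.63 SD and 2√(0.10/0.90) = 0.67 SD, and the planned 1.01 SD is larger. If they are on the same scale as the 0.06 that gives 54, they equal 4√(0.09/0.91) = 1.26 SD and 4√(0.10/0.90) = 1.33 SD, and the planned effect is smaller. The article does not say which.

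**5. Drop-out.** 62 × 0.85 = 52.7, or 26 whole completers per arm (52). The inflation that preserves 54 is 54/0.85 = 63.5, so 64. The figure 62 matches 54 × 1.15 = 62.1. Power with 52 is 0.947 (step 1).

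**The case against.** The strongest reply is that nothing was miscalculated: 54 is what a standard G*Power option returns for η² = 0.06 at 95% power and correlation 0.5. That is right. A reader might infer that the stated power is an arithmetic error, and the documents do not support that. Nor does the point rest on the correlation being absent from a condensed article, since the full protocol may give it. It rests on what the article does state: 95% power for an effect it calls moderate, with results to be reported on another scale.

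Second, the sample-size section writes plain η² and the analysis section writes partial η², so treating them as one index is the reader's step. This stands as a condition on the 43–45%. A reader might infer that the trial has less than even odds whatever is meant, but the figure applies only if 0.06 is a partial η² for the pre-post interaction. Using three visits it is 0.62, still far from 0.95, and the stated hypothesis is about pre-post change.

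Third, the correlation may be higher than 0.5, and at 0.7 power is 99.7% on the default option. True, and both directions belong in the account. But that option holds the raw difference fixed, so at 0.7 the implied effect is 1.30 SD of change. A higher correlation does not raise power for a partial η² of 0.06.

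Fourth, a reader might infer from step 4 that the planned effect is about 1.5 times the benchmark it claims to undercut (1.01/0.67). That assumes a scale for the cited values that the article does not give; on the other scale the comparison is correct.

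Finally, the drop-out slip is two participants and under one point of power. The quoted rate is approximate (62 retains 54 at 8/62 = 12.9% loss), and a mixed model can use partial data. All of that stands, and the slip is minor.

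**Conclusion.** The point holds in this form. With 27 completers per arm, 95% power requires an arm difference in change of 1.0 SD (partial η² about 0.20), whatever convention was entered. On the partial η² scale that the trial will report, 0.06 is about 0.51 SD and has about 43–45% power for the pre-post interaction; 95% would need about 206–208 completers. The 54 rests on a correlation that is not stated and appears to be 0.5. That value is inferred from the result, so it is an assumption here. Whether the planned effect is smaller than the cited 0.09–0.10 cannot be settled from the article. The 62 enrolled miss the section's own minimum of 54 at its own drop-out rate, with a power cost of 0.954 to 0.947. The main consequence is for interpretation: a null primary result could not be said to exclude a partial η² of 0.06 with 95% power.

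**What to change.** Keep enrolment as it is and restate the paragraph:

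- State the effect-size convention and the correlation actually entered. The sponsor must supply the correlation; 0.5 should be written only if it was the value used.
- Say what the sample can detect: 54 completers give 95% power for a 1.0 SD arm difference in pre-post change (partial η² about 0.20), 80% for about 0.78 SD (partial η² about 0.13), and about 44% for partial η² 0.06.
- Drop the description of the effect as moderate. Keep the statement that it is somewhat smaller than the cited values only if those values are shown to be on the same scale.
- Correct the drop-out line: 62 enrolled with 15% drop-out is expected to give about 52 completers; 64 would be needed to keep 54.

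The cost is wording only. No test, endpoint or enrolment target changes, but the power statement becomes less favourable.
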